### 3.3 Secondary endpoints

1) Effectiveness evaluation

The secondary endpoints include comparison between the two groups on **patient outcome**:

- Length of hospital stay

- quality of life: EQ-5D^10^ (at admission, discharge, 1 month, 3 months, 6 months and 12 months post-surgery)

- functional status: Parker Mobility Score^11^, modified Barthel Index^12^, Lawton and Brody Scale^13^, Katz index (admission, discharge, 1 months, 3 months and 6 months post-surgery).

- hospital readmissions (30 and 90 days after discharge)

- falls (= “an unexpected event in which the patients comes to rest on the ground, floor or lower level”) and new fractures, either by retrospectively checking electronic patient record for any contact after discharge to any hospital or emergency department stating the occurrence of falls or new fractures) and by a questionnaire send out to patient and care givers. (admission, in-hospital, at discharge, at 1, 3, 6 months post-surgery 12 months post-surgery)

- Living situation: defined in 5 categories: living alone at home, living with spouse/partner, living with children, assisted living, living in a facility with 24h care such as nursing home). Details of care provided will be recorded as one of the following categories: 24h care, daily, irregular, no care. (admission, discharge, 1 month, 3 months post-surgery, 12 months after surgery)

- mortality (in-hospital, 1 month post-discharge and 12 months after discharge)

- secondary fracture prevention: documentation of fall risk assessment, medication review of calcium/vitamin D use and osteoporosis treatment, appointment to fracture liaison service (12 months after surgery)

- nutritional status: Mini Nutritional Assessment (MNA) ^14^ (at admission, 1 month, 3 months and 6 months post-surgery)

- cost-benefit analysis:

Costs will be assessed using a model that registers key hospital activities from the electronic patient record (KWS): 'beeldvorming', 'daghospitalisatie', 'dialyse', 'functiemeting', 'hospitalisatie', 'hospitalisatie ITE', 'labo', 'operatiekwartier', 'paramedische staf', 'raadpleging', 'raadpleging functiemeting', 'radiotherapie', 'spoedgevallen'. The model was developed by UHL.

2. Feasibility evaluation (is the intervention successfully implemented?):

2.1:

- the reach of the program (% of all eligible patients that were included in the G-COMAN program, defined as the patients who completed the questionnaire)

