### 3.4 Trial Design

single-centre pre-post implementation study on the traumatology ward of the University Hospitals Leuven

**Usual care (pre-cohort):** the control group receives usual care on the traumato ward. This means that the patient is cared for by a surgical resident. The interprofessional team furthermore consists of ward nurses, a physiotherapist, an occupational therapist and a social worker. No tailored geriatric protocols are available to the traumato team, except for those that are available hospital-wide for all patients (e.g. fall prevention, delirium). Geriatric expertise is available upon active request by the traumato team and includes the comprehensive evaluation of the patient by a geriatric nurse (consultation model).

Due to the design of the G-COMAN strategic project and its predefined strict timing schedule (a phased implementation with the need of a rapidly full implementation), the timeframe for inclusion of the pre-cohort is limited. At the end of the pre-cohort, the predefined sample size will not be reached. To obtain sufficient included patients in the pre-cohort, this patient cohort will be supplemented with patients of which retrospectively information will be gathered. This results in a pre-cohort that will be partly prospective and partly retrospective.

**Geriatric co-management intervention, quality-improvement project G-COMAN (post-cohort):** A dedicated traumato nurse (G-COMAN nurse) will systematically perform a frailty screening in all newly admitted older patients on the traumato ward to evaluate if they are to be included in the G-COMAN program. In eligible patients, a comprehensive geriatric assessment (CGA) will be performed by the G-COMAN nurse. Based on identified potential problems, a tailored care plan based on predefined geriatric protocols will be launched. As part of the project a geriatric specialist nurse will provide every weekday training and education of the G-COMAN nurse and other team members on the traumato ward. The implementation of automated care plans and predefined geriatric protocols will be coordinated by a G-COMAN project coordinator, as well as the organisation of focus groups and intervisions to ensure smooth and supported collaboration.

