3.6 Trial Flowchart

### *Baseline variables and effectiveness outcomes including time points in the prospective pre- and post-cohort and retrospective pre-cohort.*

| **Variable** | **Instrument** | **Description** | **Score** | **Type of assessment** | **Prospective pre-cohort/post-cohort** | | | | | | **Retrospective pre-cohort** |
| --- | --- | --- | --- | --- | --- | --- | --- | --- | --- | --- | --- |
|  |  |  |  |  | **Admission** | **Discharge** | **1M FU** | **3M FU** | **6M FU** | **12M FU** | **Yes/No** |
| Demographics | N/A | Age, gender |  | Record | X |  |  |  |  |  | Yes |
| Comorbidities | Age-adjusted Charlson Comorbidity Index | Assessment of 16 medical conditions scored based on severity and age | 0-37 | Record | X |  |  |  |  |  | Yes |
| Activities of Daily Living (ADL) | Katz index | Bathing, dressing, toileting, transferring, continence, feeding | 6-18 | Questionnaire | X | X | X | X | X |  | Only baseline via record |
|  | Modified Barthel index | Bowels, bladder, grooming, toilet use, feeding, transfers, mobility, dressing, stairs, bathing | 0-100 | Questionnaire | X | X | X | X | X |  | Only baseline via record |
| Instrumental ADL | Lawton and Brody scale | Telephone use, shopping, food preparation, housekeeping, laundry, mode of transportation, medication use, finances | 0-8 | Questionnaire | X | X | X | X | X |  | Only baseline via record |
| Nutritional status | Mini nutritional assessment | 6 screening questions | 0-14 | Questionnaire | X |  | X | X | X |  | Only baseline via record |
| Mental status | Mini-cog | Three-item word memory and clock-drawing | 0-5 | Test | X | X |  |  |  |  | Only baseline via record |
| Injury and surgery details | N/A | Type of fracture  Type of surgery  Time to surgery  ASA score |  | Record |  | X |  |  |  |  | Yes |
| In-hospital complications | N/A | Delirium  Congestive heart failure  Pneumonia  Deep venous thrombosis  Pulmonary embolism  Myocardial infarction  Urinary tract infection |  | 4AT  Record |  | X |  |  |  |  | Yes, record |
| Length of hospital stay | N/A |  |  | Record |  | X |  |  |  |  | Yes |
|  |  |  |  |  |  |  |  |  |  |  |  |
| Unplanned readmissions | N/A |  |  |  |  |  | X | X |  |  | Yes |
| Mortality | N/A |  |  | Record |  | X | X |  |  | X | Yes |
| Living situation | N/A |  |  | Questionnaire | X | X | X | X |  | X | Only baseline and discharge via record |

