### 6 months after discharge

Patients or their care givers will receive a letter by post with instructions and an assessment questionnaire for follow-up assessment at 1 month post discharge. In case of no response, the researchers will contact the patient / care giver by telephone to complete the assessment. The following items will be evaluated: **functional status** (Parker Mobility Score, Barthel Index, Lawton and Brody Scale, Katz index), **Quality of Life** (EQ-5D), **nutritional status**, and the **presence of new falls and fractures** as well as the use of calcium/vitamin D and anti-osteoporosis **medication in a questionnaire**. None of the variables can be retrospectively collected.

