### 8.2 Analysis

Pre- and post-cohort: Categorical data will be expressed as numbers and percentages. Continuous data will be expressed as means with standard deviations. Baseline characteristics will be described and compared between usual care and intervention group to evaluate the baseline equivalence. If equivalent we will test the absolute difference for our primary outcome ‘in-hospital complications’ between the two groups (t-test). If not equivalent, we will test the mean number of in-hospital complications in both groups.

Non-parametric tests will be used to compare baseline characteristics between patients who are losted to follow-up from the control and intervention group. A missing data analysis (multiple imputation) will be performed for baseline characteristics.

In addition, univariable and multivariable regression models will be used whereby the outcome will be the number of in-hospital complications. Following baseline characteristics will be used to control for potential baseline confounding: age, gender, functional status pre-fracture (Katz ADL), physical performance (Parker Mobility score pre-fracture, grip strength), cognitive status (Mini-Cog), multimorbidity (Charlson Comorbidity Index) and nutritional status (Mini Nutritional Assessment).

Secondary analyses will consist of univariable statistical tests (chi^2^ or Fisher’s exact test for categorical variables; t-test or Wilcoxon rank-sum test for continuous variables) to evaluate differences between the two treatment groups. Logistic regression will be used for dichotomous outcomes, survival analyses for time to event variables (with mortality defined as a competing risk for the outcome readmission), and ANCOVA for mean inter-group differences

Longitudinal data will be analyzed by means of mixed effects regression models to estimate differences in mean scores (eg. EQ-5D, modified Barthel Index, Parker Mobility Score, Lawton and Brody Scale) between follow-up and the respective baseline assessment by treatment group. Statistical significance is established at p-value < 0.05.

Enrolled patients who withdraw from the study follow-up for any reason (withdrawal of consent, death, loss of follow-up, …) will be included in the analyses until time at which they withdrew.

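### For function and nutrition scores, retrospective controls have a record-derived baseline and no follow-up, and section 8.2 does not keep them out of the longitudinal models

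*Protocol*

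**What the plan says.** Section 3.4 explains that prospective recruitment of usual-care patients will stop short of the target and that the shortfall will be filled from existing records: "This results in a pre-cohort that will be partly prospective and partly retrospective". The split is not given.

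Section 3.3 sets the purpose of the repeated scales: "The secondary endpoints include comparison between the two groups". Section 8.2 gives the method: "Longitudinal data will be analyzed by means of mixed effects regression models to estimate differences in mean scores", taken "between follow-up and the respective baseline assessment by treatment group". It names EQ-5D, modified Barthel, Parker and Lawton-Brody as examples. Katz and the nutritional score are not named there, but the flowchart schedules them repeatedly too. Nothing in 8.2 limits these models to patients who were followed.

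The flowchart in 3.6 has a separate column for the retrospective controls. For Katz, modified Barthel, Lawton-Brody and the nutritional score it reads "Only baseline via record", whereas prospective and post-cohort patients answer a questionnaire at admission and at follow-up. EQ-5D is marked as not collected in retrospective controls. The Parker score has no row, but the baseline part of 5.1 says that every baseline variable other than quality of life can be taken from the record.

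The visit descriptions in 5.1 list no retrospective functional or nutritional score after baseline. The six-month entry is the plainest: "None of the variables can be retrospectively collected".

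**The concern.** Three things that the protocol fixes do not fit together: who the control group is, what is measured on each part of it, and which contrast the model estimates. If the control group in 8.2 is the one defined in 3.4, the retrospective patients add to the control baseline and never to the control follow-up. Their baseline also comes from a chart entry, whereas the prospective patients are asked about their pre-injury state.

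The post-cohort has no retrospective part, so a systematic difference between the two kinds of baseline would not cancel in the group comparison. It would pass into the estimated programme effect on functional and nutritional status, both of which the synopsis lists among the outcomes on which superiority is to be shown.

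**Working it through.** **The plan's own figure.** The only sample size in the protocol is 108 per group, for complications (8.1). It can be reached from the stated inputs: 71% versus 51%, two-sided 0.05, 80% power, with continuity correction, gives 102 per group, and 102 / 0.95 = 107.4, rounded up to 108. The point does not depend on this number. It matters only because no smaller control number is stated for the scales discussed here.

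**What retrospective controls contribute** (3.6 and 5.1)

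| Scale | Baseline | Follow-up | Effect on the control change |
|---|---|---|---|
| Modified Barthel, Lawton-Brody, Katz, nutritional score | from record | none | mixed if these patients are included |
| Parker | from record (5.1) | none | mixed if these patients are included |
| EQ-5D | none | none | not mixed; fewer controls |

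Mortality and readmission are collected retrospectively, so the absence of follow-up concerns the modelled scores only.

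**Size of the shift if they are included.** Take one baseline and one follow-up, with these assumed quantities, none of which the protocol gives:
- s: retrospective share of controls
- b: within-patient correlation, equal to the slope of follow-up on baseline when the variances are equal
- d: record-derived baseline mean minus questionnaire baseline mean

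1. The control baseline mean is estimated from all controls, so it moves by s × d.
2. The likelihood carries the baseline of unfollowed patients into the follow-up mean through the slope, so the follow-up mean moves by b × s × d.
3. The control change (follow-up minus baseline) moves by b × s × d − s × d = −s × (1 − b) × d.
4. The post-cohort change does not move, so the group-by-time effect (post minus control) moves by +s × (1 − b) × d.

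Shift per unit of d:

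| s | b = 0.7 | b = 0.5 | b = 0.3 |
|---|---|---|---|
| 0.25 | 0.075 | 0.125 | 0.175 |
| 0.50 | 0.15 | 0.25 | 0.35 |
| 0.75 | 0.225 | 0.375 | 0.525 |

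For illustration on the 0–100 modified Barthel, with s = 0.5 and b = 0.5 to 0.7:
- d = 0 gives no shift
- d = 5 gives 0.75 to 1.25 points
- d = 10 gives 1.5 to 2.5 points

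**Check by simulation.** A random-intercept model was fitted to simulated data with 108 per group, an assumed SD of 20, b = 0.5, s = 0.5 and no true effect (150 repetitions). The mean group-by-time effect was 0.1, 1.2 and 2.7 points at d = 0, 5 and 10. The formula gives 0, 1.25 and 2.5.

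**The case against.** The strongest reply is that 8.2 never says baseline-only patients enter these models. Its reference to the respective baseline can be read as pairing each patient's follow-up with that patient's own baseline, in which case someone without follow-up contributes nothing. The set of patients in a secondary model is also often left to an analysis plan, and the protocol is open about the limits of retrospective collection in 3.6 and 5.1. What stands of this is that the distortion is conditional. But the text does not exclude these patients, and no other rule in 8.2 settles the matter. The withdrawal rule concerns enrolled patients who leave follow-up, whereas these scores are missing by design. Multiple imputation is planned for baseline characteristics only.

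A second reply is that a mixed model keeps the within-patient pairing, and that there is no distortion if the two kinds of baseline are exchangeable. Both statements are correct. The factor (1 − b) reflects the first, and the shift vanishes at d = 0. The documents give no evidence of a gap. The different method and the different source of patients only make equality something that should not be taken for granted.

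A reader might also infer that the plan estimates only change within each group. The documents do not support that: 3.3 calls for a comparison between the groups, 8.2 names ANCOVA for inter-group differences, and change by group in a mixed model is naturally read as a group-by-time comparison.

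**Conclusion.** The point holds for modified Barthel, Lawton-Brody, Katz, the nutritional score and Parker. As written, only the control group's baseline can mix in other patients and another measurement method. If it does, the control change shifts by about s × (1 − b) × d: 0.15 d to 0.25 d at s = 0.5 and b = 0.5 to 0.7, and nothing at d = 0. All three quantities are assumptions, so this describes how the error would scale. It does not show that the result will be biased.

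Two stronger readings should be resisted. EQ-5D, although named first in 8.2, is not mixed: retrospective controls have neither baseline nor follow-up on it, so the only consequence is a smaller control sample. Nor does that smaller sample contradict any stated power, because 8.1 powers only the complication endpoint.

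These are secondary endpoints. The change is nevertheless worth making in the protocol, because the mismatch lies between parts that the protocol itself fixes.

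**What to change.** In 8.2:
- Restrict the longitudinal models of questionnaire scales to the prospective pre-cohort versus the post-cohort.
- Define the effect as the group-by-time contrast, adjusted for the patient's own baseline and for those confounders listed in 8.2 that are actually collected. Omit grip strength unless it is measured: it is in the 8.2 list, but in neither the flowchart nor the baseline assessment in 5.1. Where Katz, Parker or the nutritional score is the outcome, do not enter its baseline a second time as a confounder.
- Use record-derived baselines only descriptively or in a sensitivity analysis.
- State that the control number for these endpoints, EQ-5D included, is the prospective part of the pre-cohort and therefore below 108.

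The cost is protocol wording and a smaller stated control number. No follow-up data are lost, because the patients left out have none on these scales.

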# Background and rationale

Osteoporosis is the most common musculoskeletal disease and predisposes to fractures of hip, spine, proximal humerus, pelvis and wrist. Approximately around 80.000 fragility fractures occurred in Belgium in 2010 – with associated costs estimated at 606 million euros ^1^. Based on demographic forecasts it is predicted that by 2050 the number of hip fractures will have more than doubled from 2015^2^. These fragility fractures are **associated with pain, disability, need for institutionalization and even death** ^3^. The complex needs of the older fracture patient with multimorbidity, polypharmacy and geriatric syndromes require a holistic, multidisciplinary approach ^4^. This is the expertise of geriatricians and geriatric teams.

At the moment there is little cooperation between geriatricians and surgeons in Belgium due to the current care organization with silo financing. Moreover effects of geriatric consultation teams (as installed by Royal Decree in 2007, update in 2014) are quite limited as repeatedly observed in literature, due to their reactive nature and lack of implementation of advice given^5^. Hence, focus in literature has shifted to different forms of collaboration, such as **co-management with proactive care and shared responsibility** between geriatric and non-geriatric team members. This co)management model can have a significant impact on hospital stay, in-hospital complications and mortality^6^. Based on this convincing data the National Health Service (UK) has **incorporated geriatric care into its guidelines** and hospital reimbursement policy (Best Practice Tariff) resulting in a spectacular nationwide reduction in mortality of hip fracture patients^7^.

Some years ago, we successfully introduced a geriatric co-management model on the cardiology department in our hospital (G-COACH) with significant and clinical relevant results; a reduction in functional deterioration by 18%, better functional status at hospital discharge (Katz ADL 8.9 vs 9.5 in usual care), 13% less delirium and significant fewer nosocomial infections^8^.

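### Section 8.2 groups death with withdrawal and treats it as a competing risk only for readmission, so the 12-month comparisons of falls, fractures and EQ-5D depend on any mortality difference

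*Protocol*

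**What the plan says.** Section 8.2 (Analysis) gives one rule for enrolled patients who leave follow-up "for any reason (withdrawal of consent, death, loss of follow-up" and other causes: they "will be included in the analyses until time at which they withdrew". The same section recognises death as an event that precludes another, but for one outcome only: survival analyses are planned "with mortality defined as a competing risk for the outcome readmission". Under section 3.3, readmission is assessed at 30 and 90 days after discharge.

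Other secondary outcomes run longer. In section 3.3, falls and new fractures are recorded up to 12 months ("at 1, 3, 6 months post-surgery 12 months post-surgery"), as is EQ-5D ("at admission, discharge, 1 month, 3 months, 6 months and 12 months post-surgery"). The functional scores stop at 6 months. For the scores, section 8.2 states: "Longitudinal data will be analyzed by means of mixed effects regression models". It names EQ-5D, modified Barthel, Parker and Lawton as examples and gives no rule for death. Multiple imputation is stated for baseline characteristics only. The end of section 8 acknowledges possible bias from death; the only measure it offers is caretaker help for patients who cannot complete questionnaires.

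The protocol expects mortality to respond to this kind of care. The Background describes a national policy "resulting in a spectacular nationwide reduction in mortality of hip fracture patients" and says that co-management can affect mortality. Mortality is itself a secondary endpoint.

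**The concern.** A patient who withdraws consent still has falls and a quality of life that go unobserved. A patient who has died has neither. One rule for both leaves the target of estimation undefined for every outcome that death cuts short.

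- **Falls and new fractures.** If deaths are censored or dropped, the result describes a setting in which nobody dies. It then differs from the proportion of patients who actually fall, by an amount that depends on each cohort's mortality.
- **EQ-5D and functional scores.** A mixed model treats scores after death as ordinary missing data. If the programme keeps frailer patients alive, the post-cohort's survivors include more people with low scores, and a real benefit can look like no effect or harm.

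The protocol applies competing-risk handling to an outcome observed for 90 days and not to outcomes observed for a year, by which time more patients will have died.

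**Working it through.** The documents give no mortality, fall, EQ-5D or length-of-stay rates, so every input in steps 2 to 4 is an assumption used to show direction and order of size.

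**1. The plan's own figure.** The only number in section 8.1 is 108 per group, for the primary endpoint. It is reproducible. For 71% versus 51% (two-sided 0.05, power 0.80), the two-proportion formula with continuity correction gives 102, and 102 / 0.95 = 107.4, rounded up to 108. The present point does not depend on it.

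**2. Falls.** Assume constant, independent hazards over 12 months, with the same fall hazard in both cohorts. Let F be the 12-month fall risk without death and D the 12-month mortality; lf = −ln(1 − F), ld = −ln(1 − D). Censoring at death returns F in both cohorts, and so does restricting to 12-month survivors. The proportion who actually fall is

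CIF = lf / (lf + ld) × [1 − (1 − F)(1 − D)].

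For F = 30%, lf = 0.357:
- D = 25%: ld = 0.288; CIF = 0.357/0.644 × 0.475 = 26.3%.
- D = 15%: ld = 0.163; CIF = 0.357/0.519 × 0.405 = 27.8%.

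| F (estimate if deaths censored, both cohorts) | CIF at D = 25% | CIF at D = 15% | Gap |
|---|---|---|---|
| 10% | 8.7% | 9.2% | 0.5 points |
| 30% | 26.3% | 27.8% | 1.5 points |
| 40% | 35.2% | 37.2% | 2.0 points |

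With mortality of 30% versus 20% the gaps are 0.5, 1.6 and 2.0 points. With 20% in both cohorts the gap is 0. Excluding only those who died without a recorded fall is a further variant, which this range does not cover.

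For scale, the standard error of a difference with 30% fallers and 108 per group is √(2 × 0.3 × 0.7 / 108) = 6.2 points, so a 1.5-point shift is about a quarter of it.

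**3. EQ-5D.** Two illustrations, neither of them a mixed-model fit.

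(a) Simulation with no true effect on the score: mean 0.60, SD 0.25, correlation 0.5 with a frailty variable that also drives death.

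| Mortality, pre vs post | Survivor means | Difference | Means with death = 0 | Difference |
|---|---|---|---|---|
| 25% vs 15% | 0.627 vs 0.617 | −0.010 | 0.470 vs 0.525 | +0.054 |
| 30% vs 20% | 0.632 vs 0.622 | −0.010 | 0.442 vs 0.498 | +0.055 |
| 20% vs 20% | 0.622 vs 0.622 | 0.000 | 0.498 vs 0.498 | 0.000 |

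(b) By hand: mortality 25% versus 15%, control survivors at 0.60, the extra 10% of survivors at 0.35. Survivor mean in the post-cohort: (0.75 × 0.60 + 0.10 × 0.35) / 0.85 = 0.571, against 0.60. With death as 0: 0.485 against 0.75 × 0.60 = 0.450.

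Both show a sign change between the two summaries. The survivor difference itself depends on the inputs: −0.010 in (a), −0.029 in (b).

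**4. Length of stay.** Assume 12 days for survivors and 7 days when the stay ends in death. The spurious difference is (in-hospital mortality difference) × 5 days: 6% versus 3% gives 0.15 days, 8% versus 4% gives 0.20 days.

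**5. Who contributes.** In section 3.6 the retrospective part of the pre-cohort has no EQ-5D, functional scores at baseline only, and falls at baseline and discharge only. Steps 2 and 3 therefore concern prospectively followed patients.

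**The case against.** The rule in section 8.2 says which data are kept; it does not say that death is uninformative censoring. No data exist after death, so using a patient's data up to that date is unavoidable. Falls are never assigned to survival analysis. They are collected at fixed time points, and section 8.2 equally allows chi-square or logistic regression. If every enrolled patient stays in the denominator, a death without a fall counts as no fall, which is the cumulative incidence wanted. Cause-specific and while-alive targets are legitimate, and handling of death by outcome is often left to the statistical analysis plan.

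Much of this stands, and it is why the falls point is conditional on deaths being censored or dropped. It does not remove the point. The protocol does more than stay silent: it puts death under the withdrawal rule in writing, makes one exception, and declares no target that would justify the rest.

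Four stronger readings are tempting but unsupported:
- **A 4 to 6 point error in falls.** At F = 40% the overstatement within a cohort is 40 − 36.2 = 3.8 points at 20% mortality and 40 − 34.2 = 5.8 points at 30%. Most of it cancels between cohorts, leaving about 2 points.
- **A biased length of stay.** "Length of hospital stay" is listed as an endpoint, but the withdrawal rule concerns study follow-up, and no text says how a stay that ends in death is counted. The assumed shift is small.
- **A predicted reversal in the mixed model.** The figures in step 3 are survivor means under assumed inputs, so they show only that a reversal is possible.
- **Death mishandled everywhere except readmission.** Mortality is analysed as an endpoint in its own right.

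**Conclusion.** The point holds in limited form, for secondary outcomes. Section 8.2 pools death with withdrawal and limits competing-risk handling to readmission. If the programme changes mortality, the comparison of falls and new fractures shifts by about 0.5 to 2 points when deaths are censored or dropped, assuming a 10-point difference in 12-month mortality and independent constant hazards. The EQ-5D and functional comparisons become comparisons among differently selected survivors, and the sign of the EQ-5D difference can depend on how death is valued. With equal mortality these between-group distortions are about zero. EQ-5D is the stronger part; the falls shift is small against sampling error. The primary endpoint and the sample size are unaffected. The change is worth making because the protocol itself anticipates a mortality effect and the correction is cheap.

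**What to change.** In section 8.2:
- Remove death from the list of withdrawal reasons and state its handling separately.
- Extend the existing competing-risk rule from readmission to new falls and new fractures. Where only presence by a time point is known, keep patients who died without an event in the denominator as having no event; do not censor or drop them.
- Describe the mixed-model results for EQ-5D and the functional scores as conditional on being alive.
- Add one supplementary EQ-5D analysis with value 0 from death onward.
- For length of stay, at most add a sensitivity analysis of time to discharge alive, with in-hospital death as a competing event.

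The cost is wording and a few extra analyses. Mortality is already taken from the electronic record to 12 months; the date of death should be kept so that status at 3 and 6 months is known. Section 5.1 asks about the presence of falls and does not mention dates, so a full time-to-event analysis may not be possible for falls; the fixed-time-point rule above covers that case. The death-as-0 analysis answers a slightly different question and should stay supplementary.
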